### Randomisation

A computer-generated randomisation sequence will be used to assign the participants to the intervention and waitlist-control arms in a 1:1 ratio. Block randomisation of block sizes 4 or 6 will be generated in a computerised randomisation schedule. Randomisation will take place after pre-intervention data collection. The allocation sequence will be concealed using an online central randomisation service set up and maintained by a professional third party (www.sealedenvelope.com) that will conceal the sequence until group assignment. The randomisation process will require the research team to either (1) log into a password-protected website or (2) send a Short Message Service (SMS) message and enter the relevant data of each newly recruited participant in order to receive the allocation.

### Blinding

Randomisation will take place in the community, at scheduled group ‘information and assessment’ meetings, directly after pre-intervention data collection. The research team will oversee the randomisation process. Participants will not be blinded to group allocation; they will be informed of group allocations immediately at the group meeting, along with local TRT group leaders. Allocation status will be recorded on a secure online platform (www.sealedenvelope.com). Data collection will not be blinded; however, as the outcome data is collected using self-completion questionnaires rather than through observation or interview, outcome data is less susceptible to information bias and interviewer effects [9]. Given that neither the participants nor group leaders are blinded, there is no requirement for an unblinding procedure. Outcome data spreadsheets will use anonymous participant identity numbers; however, group status will be apparent due to the inclusion of attendance data for the intervention group.

### Control arm

Youth assigned to the waitlist-control arm will receive services as usual because the aim of the trial is to determine whether the TRT programme provides added value. The offer is likely to include school health services and contact with their general practioner (GP). Other services are unlikely to be highly similar to the TRT programme, as reconnaissance suggests that typically few group therapy programmes are available for unaccompanied refugee youth. Any services that youth do receive, including other therapy programmes, will be captured in the Trimbos/institute for Medical Technology Assessment (iMTA) Questionnaire for Costs associated with Psychiatric Illness (TiC-P) (see Other measures section).

### Intervention arm

The intervention arm will receive the Swedish translation of the TRT programme and may access services as usual. The intervention uses TF-CBT as its foundation, agreed to be the method of choice for treating PTSD in children and adolescents [15]. The group-based cognitive behavioural programme includes five youth sessions and two caregiver sessions. A ‘getting to know each other session’ will be offered prior to the core TRT sessions and a ‘follow-up session’, which consolidates learning and enables participants to talk about their experience of taking part in the programme, will be offered afterwards. Sessions will be delivered over 7 consecutive weeks. Each session will last 2 h (including a break). For unaccompanied refugee youth, the ‘caregiver’ is a nominated adult (e.g. their legal guardian, an adult from their family home or a school counsellor). The sessions for youth incorporate several components of TF-CBT, including psychoeducation, affective modulation skills, cognitive coping and processing, trauma narrative, overcoming trauma reminders and future development. The caregiver sessions include an introduction to the TRT method and an overview of the content in the youth sessions. The caregivers are instructed in how to support the youth through listening and comforting, when needed, as well as through maintaining routines and activities. Additionally, the caregivers receive information on how to seek care if the youth needs additional help after TRT. Caregiver sessions are delivered without the youth, in parallel with the first two youth sessions. TRT group leaders receive 3 days of training in programme delivery from BRIS (Children’s Rights in Society). Two group leaders deliver each group (with the assistance of an interpreter, if necessary).

### Participant timeline

A schedule of enrolment, interventions and assessments is shown in Fig. 1 and a flow diagram of the participant timeline is shown in Fig. 2. Youth are screened for eligibility, which could be done individually or at a group ‘information and screening’ meeting. For eligible youth, informed consent and pre-intervention assessments take place at a group ‘information and assessment’ meeting. A case will be randomised once the participant has completed all pre-intervention data collection. Follow-up data will be collected from all participants at scheduled group meetings at two points: first (T2), about 8 weeks (+/− 1 week) after randomisation (equivalent to end of TRT programme delivery), and second (T3), about 20 weeks (+/− 2 weeks) after randomisation (equivalent to about 3 months after TRT programme delivery).

**Fig. 2 Fig2:**
[figure not shown]
SUPpORT participant flow chart

### Outcome measures

The study will primarily measure changes in youth self-reported mental health, specifically symptoms of PTSD, depression and anxiety. A combination of primary mental health measures is being used due to the complex trauma that can be experienced by the youth. Apart from adverse events before and during migration, the asylum and resettlement process per se involves stressors. Complex trauma can lead to social difficulties, behavioural and emotional symptoms, psychosomatic problems and sleep problems as well as PTSD symptoms [11, 22, 33].

Secondary assessments will include measures of self-efficacy and well-being, both of which relate to the TRT programme theory of change. All outcome measures will initially be available in Swedish, English, Arabic, Dari, Farsi, Somali and Tigrinya, with other languages made available if necessary. The measures will be administered pre-intervention (T1), after intervention delivery (T2) and a few months later (T3). The specific metrics, methods of aggregation and time points for the outcomes are described in the Statistical methods section.

#### Children’s Revised Impact of Event Scale (CRIES-13)

The CRIES-13 [21] is a 13-item self-report measure of PTSD symptoms. Individual items are rated according to the frequency of their occurrence during the past week (None = 0, Rarely = 1, Sometimes = 3, and A lot = 5) and in relation to a specific traumatic event. Scores are obtained for 4 intrusion items (e.g. *Do you think about it even when you don’t mean to?*), 4 avoidance items (e.g. *Do you try not to talk about it?*) and 5 arousal items (e.g. *Do you get easily irritable?*). Total scores on the scale range from 0 to 65 with a cutoff score of 30 or above. The total score has been shown to have good internal consistency, and to successfully categorise more than 75% of children with and without a PTSD diagnosis [21, 42]. In a study of asylum-seekers in Sweden, the CRIES-8, a shorter version of CRIES which only includes the intrusion and avoidance items, was shown to have good internal consistency (Cronbach’s α = 0.75), and its factor structure was confirmed [27].

#### Patient Health Questionnaire-9 (PHQ-9)

The PHQ-9 [16] is a 9-item self-report instrument for screening, diagnosing, monitoring and measuring severity of depression. Individual items (e.g. *Little interest or pleasure in doing things*) are rated according to the frequency of their occurrence during the past 2 weeks (Not at all = 0, Several days = 1, More than half the days = 2, Nearly every day = 3). Total scores on the scale range from 0 to 27 with cutoff scores of 5, 10, 15 and 20 for mild, moderate, moderately severe and severe symptoms respectively. The instrument has shown high internal consistency, with Cronbach’s α = 0.86 and 0.89 in two primary care samples respectively, and test-retest reliability *r* = 0.84 [16]. Both construct validity and diagnostic validity for major depression have been established in several studies, and sufficient sensitivity (0.71–0.87) and high specificity (0.88–0.95) have been found for PHQ-9 ≥ 10 [12]. PHQ-9 has also been shown to be responsive in measuring treatment outcomes, and a change in scores of 5 has been suggested to reflect a clinically relevant change [18].

#### Generalised Anxiety Disorder-7 (GAD-7)

The GAD-7 [35] is a 7-item self-report measure originally developed to screen for generalised anxiety disorder. It has, however, also frequently been used to assess severity of more general anxiety symptoms [17]. Individual items (e.g. *Feeling nervous, anxious, or on edge*) are rated according to the frequency of their occurrence during the past 2 weeks (Not at all = 0, Several days = 1, More than half the days = 2, Nearly every day = 3). Total scores on the scale range from 0 to 21 with cutoff scores of 5, 10 and 15 for mild, moderate and severe symptoms respectively. It has shown high internal consistency (Cronbach’s α = 0.92) and seems to function well as an indicator of symptom severity [35].

#### General Self-Efficacy Scale (GSE)

The GSE [30] is a 10-item self-report measure that assesses the strength of individuals’ beliefs in their own ability to respond to difficult situations and to deal with obstacles or setbacks. Individual items (e.g. *I can always manage to solve difficult problems if I try hard enough*) are rated according to how true the statement is for that individual (1 = Not at all true, 2 = Hardly true, 3 = Moderately true, 4 = Exactly true). Total scores range from 10 to 40 with a higher score indicating more self-efficacy. In samples from 25 nations, Cronbach’s α ranged from 0.75 to 0.91 [29].

#### The Cantril Ladder

The Cantril Ladder [6] measures well-being and life satisfaction. The respondents are presented with a picture of a ladder numbered from 0 to 10, where the bottom of the ladder (0) represents their worst possible life and the top (10) represents the best. Respondents are asked to think about their life right now and place themselves on the ladder. Total scores range from 0 to 10 with a higher score indicating greater well-being and life satisfaction. A score of 4 or below is indicative of ‘suffering’ and 7 or above ‘thriving’. The scale has proven a valid measure of general psychosocial health among children/youth of ages 10–17 years [19]. The Cantril Ladder will be administered at each TRT session to inform a safety protocol. The total score will be used as a secondary outcome, assessed at T1, T2 and T3.

### Other measures

Basic demographic information and trauma history will be collected for all participants. Health-related quality of life and service consumption will be measured to inform the economic evaluation. A suicidality screening tool will be utilised as part of a safety protocol for participants who indicate they have had thoughts they would be better off dead (ninth item on PHQ-9) or ‘suffering’ on the Cantril Ladder (i.e. a score of 4 or below).

#### Demographics questionnaire

The study will use a short questionnaire to gather demographic information about the youth and his/her family. It includes variables such as youth age, gender, ethnicity, time spent in Sweden and asylum status. This data will be used to describe the sample, examine the extent to which demographic characteristics are balanced between trial arms, carry out attrition analyses (i.e. the extent to which participants who drop out from the intervention and waitlist-control arms are different on variables such as gender and ethnicity) and identify subgroups. The demographics questionnaire will be administered pre-intervention (T1). A brief version of the questionnaire that includes items for which the response may change (e.g. asylum status) will be administered after intervention delivery (T2) and a few months later (T3).

#### Refugee Trauma History Checklist (RTHC)

The RTHC [31] is a self-report measure of the occurrence of potentially traumatic experiences. It consists of 2 × 8 items, concerning potentially traumatic experiences that occurred before and during the respondent’s flight respectively. Results show low item non-response and adequate psychometric properties [31]. These data will be used to describe the sample, examine the extent to which potentially traumatic experiences are balanced between trial arms, carry out attrition analyses (i.e. the extent to which participants who drop out from the intervention and waitlist-control arms report different experiences) and identify subgroups. The RTHC will be administered pre-intervention (T1).

#### Child Health Utility 9D (CHU-9D)

The CHU-9D [36] is a self-report measure of health-related quality of life. It consists of 9 dimensions (worry, sadness, pain, tiredness, annoyance, school, sleep, daily routine and activities). Individual items are scored according to severity on the day from 1 (no problems) to 5 (severe problems). Originally developed for application with children aged 7–11 years [37–39], its practicality and validity in adolescents aged 11–17 years has also been demonstrated [7, 26]. In this study, responses to the CHU-9D will be scored using the UK scoring algorithm (the only available European algorithm). The scoring algorithm was generated on a utility scale and ranges from 0 for the worst health state to 1.0 for the best health state. These scores will be used to generate quality-adjusted life years (QALYs) over the trial period, and will inform the economic evaluation. The CHU-9D will be administered pre-intervention (T1), after intervention delivery (T2) and a few months later (T3).

#### Trimbos/institute for Medical Technology Assessment (iMTA) Questionnaire for Costs associated with Psychiatric Illness (TiC-P) Child and adolescent version

The TiC-P is a self-report measure of resource use for people with a psychiatric disorder. It is a generic questionnaire, meaning that the items are not related to a target disorder. Distinguishing between health care consumption and productivity losses as a consequence of the target disorder and comorbidity is difficult, especially in psychiatric disorders, as patients also may have physical symptoms that are connected to the psychiatric illness. Moreover, psychiatric comorbidity is a common occurrence in psychiatric illness. The TiC-P will ask about service contacts and absence from school/work over a time period preceding the date of the data collection. It will be administered pre-intervention (T1), after intervention delivery (T2) and a few months later (T3) and will inform the economic evaluation.

#### Columbia-Suicide Severity Rating Scale (C-SSRS) Screen Version

The C-SSRS Screen Version [24] is a 6-item structured interview or self-report measure that assesses the presence and severity of suicidal ideation and behaviour. Individual items (e.g. *Have you wished you were dead or wished you could go to sleep and not wake up?*) are rated according to presence over the past month (Yes or No). A positive response to item 3 (*Have you been thinking about how you might do this?*) indicates a moderate risk. A positive response to item 4 (*Have you had these thoughts and had some intention of acting on them?*), 5 (*Have you started to work out or worked out the details of how to kill yourself? Do you intend to carry out this plan?*) or 6 (*Have you ever done anything, started to do anything, or prepared to do anything to end your life?*) indicates a high risk. A three-site study including both adults and adolescents showed strong convergent validity with other established scales measuring suicidal ideation and attempts [24]. Cronbach’s α varied between 0.95 for intensity of suicidal ideation during the past week and 0.73 across all visits. The C-SSRS will be utilised as part of a safety protocol for participants who indicate they have had thoughts they would be better off dead (ninth item on PHQ-9) or ‘suffering’ on the Cantril Ladder (i.e. a score of 4 or below). The safety protocol details when and where to signpost or refer to another service and has been adapted to align with service availability in local areas. Safety protocol utilisation will be captured on the fidelity checklist (see the following discussion). Frequency of safety protocol use will be reported. Any spontaneously reported adverse events will be recorded and managed accordingly by a trained member of the trial team (medical, clinical psychology and psychiatry expertise on the team).

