## Methods

### Design

A two-arm randomised waitlist-control superiority trial (1:1 allocation ratio) will be conducted to evaluate the effectiveness of the TRT programme in improving mental health outcomes in unaccompanied refugee youth who have self-reported symptoms of PTSD. The intervention arm will be offered the TRT programme immediately after randomisation and the waitlist-control arm around 20 weeks later; both trial arms will have access to services as usual. Assessments will take place at three points: pre-intervention (T1), post-intervention (T2; about 8 weeks after randomisation) and follow-up (T3; about 20 weeks after randomisation). See Fig. 1 for an overview of assessments. The Standard Protocol Items: Recommendations for Interventional Trials (SPIRIT) checklist is presented in Additional file 1.

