### Intervention fidelity

A fidelity-monitoring tool has been developed by the CHAP research team in association with TRT group leaders in order to promote and monitor adherence to the core design of the programme. The fidelity-monitoring process will be implemented by TRT group leaders, who will share the data with CHAP for research purposes. After each TRT session, the group leaders complete a self-report adherence checklist, which captures group leader details; number of participants; use of interpreter(s); number of people who required the safety protocol; and the range of core components delivered. Session attendance lists will also be shared with CHAP to inform individual participant dose.

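### The named record of safety-protocol use covers TRT sessions only, so up to T3 the reported frequency misses all assessment-visit activations and all waitlist use and cannot support a between-arm safety statement

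*Protocol article*

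**What the plan says.** The C-SSRS section of the protocol article says that "Safety protocol utilisation will be captured on the fidelity checklist" and then that "Frequency of safety protocol use will be reported". The Intervention fidelity section defines that tool: "After each TRT session, the group leaders complete a self-report adherence checklist". Among its entries is the "number of people who required the safety protocol".

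The Other measures and C-SSRS sections give two triggers: a positive ninth item on the PHQ-9, or a Cantril Ladder score of 4 or below. Neither is limited to one arm. The Outcome measures section has both instruments completed at T1, T2 and T3. The Cantril Ladder section adds a further use: "The Cantril Ladder will be administered at each TRT session to inform a safety protocol".

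On timing, the Design section offers TRT to the intervention arm straight after randomisation and to "the waitlist-control arm around 20 weeks later", which is also when T3 falls. In the intervention arm, "Sessions will be delivered over 7 consecutive weeks".

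The only other safety record named is in the C-SSRS section: "Any spontaneously reported adverse events will be recorded".

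**The concern.** The recording tool does not match what it is meant to count. The safety protocol can be activated wherever the trigger measures are given, and that includes three assessment meetings in each arm. The tool exists only where a TRT session has taken place. Followed as written, the reported frequency leaves out every activation arising at an assessment and, during the controlled period, all use in the waitlist arm.

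Participants are aged 14 to 20 and have screened positive for PTSD symptoms, and the programme includes trauma narrative work. Readers of the results will want to know whether activations differed between arms. A frequency that is positive in one arm and absent in the other because of where the form is filled in could be misread as a harm signal. If read as a total for the trial, it would understate how often the safety protocol was used.

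The entry is also a number of people per session. As described, it does not show whether the same youth was counted at several sessions, so it cannot be turned into a number of youth affected.

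**Working it through.** The article gives no figure for safety-protocol use, so there is none to reproduce. The 109 per arm used below is the stated sample size, and it does reproduce: 64 / (1 − 0.41) = 108.5, rounded up to 109.

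**Inputs**
- TRT sessions for youth: 5 core + 1 introductory + 1 follow-up = 7, over 7 weeks (Intervention arm section).
- Assessments with both trigger measures: T1, T2 and T3 in each arm (Outcome measures section). T1 precedes randomisation (Randomisation section), which leaves 2 afterwards.
- Waitlist TRT starts around 20 weeks and T3 is at about 20 weeks (Design section). I assume that waitlist sessions begin after the T3 assessment.

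**Occasions per youth from randomisation to T3, at full attendance**

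| What is counted | TRT arm | Waitlist arm |
|---|---|---|
| Checklist only (the named tool) | up to 7 | 0 |
| Sessions plus T2 and T3 | up to 7 + 2 = 9 | 2 |
| T2 and T3 only | 2 | 2 |

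The checklist also misses activations at T1 in both arms. Those affect completeness, but they precede allocation and cannot create an imbalance.

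**Illustration under no true difference.** Let p be the chance of a trigger on one occasion, equal in both arms and independent across occasions. The article gives no value, so p is an assumption. The chance of at least one trigger in k occasions is 1 − (1 − p)^k.

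At p = 0.05:
- Checklist, k = 7: 1 − 0.95^7 = 0.302, about 33 of 109 TRT youth, against 0 on waitlist.
- All occasions, k = 9 and k = 2: 1 − 0.95^9 = 0.370 against 1 − 0.95^2 = 0.098, about 40 against 11 of 109.
- T2 and T3 only, k = 2 in each arm: 0.098 against 0.098.

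| Assumed p | Checklist: TRT vs waitlist | All occasions: TRT vs waitlist | T2 and T3 only, each arm |
|---|---|---|---|
| 0.02 | 13% vs 0% | 17% vs 4% | 4% |
| 0.05 | 30% vs 0% | 37% vs 10% | 10% |
| 0.10 | 52% vs 0% | 61% vs 19% | 19% |
| 0.20 | 79% vs 0% | 87% vs 36% | 36% |

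Only the last column is balanced when there is no effect. Adding assessment activations to the session counts does not solve the problem, because the session-level Cantril Ladder gives the TRT arm extra chances to trigger.

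**Limits of the illustration.** Sessions carry only the Cantril trigger, whereas assessments carry both, so a common p is a simplification. Occasions within one youth will be correlated. Attendance will be below 100%: treatment retention in the exploratory study was 59% (Recruitment section). The percentages show direction only. The 7 against 0 on the named tool follows from the text and the stated timing assumption.

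**The case against.** The strongest reply is that the article promises only a frequency and attaches no between-arm comparison to it. A count of how often a safety procedure was used during delivery is a coherent description of implementation, it is listed under fidelity, and repeat activations by one youth are not an error in a frequency of use. All of this stands. It does not rescue the figure, because the C-SSRS section presents it as the frequency of safety-protocol use in general, and activations at assessments are part of that use.

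A reader might infer that the trial has no comparative harm data, or that this frequency is its main harm measure. The documents do not support either reading. PHQ-9 item 9 and the Cantril Ladder are collected by participant in both arms on the same schedule. The Statistical methods section also compares between arms the proportions classed as deteriorated on CRIES-13, PHQ-9 and GAD-7. What is not stated is an arm comparison of item 9, C-SSRS results or activations.

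A reader might also count 10 trigger occasions against 3 by including T1. T1 precedes randomisation, so the post-allocation figure is up to 9 against 2. Nor is the waitlist arm missing from the checklist for good: those youth attend TRT later and can then appear on it, though after the controlled comparison has ended.

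Finally, the article does not say that the checklist is the only record, and the separate safety protocol it mentions, which is not shown, may log activations at assessments. That is possible. But the article does name a tool, who completes it and when, and that tool does not cover these activations. An activation is also not the same as a suicidality event, since a low Cantril score alone can cause one.

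**Conclusion.** The point holds as a defect in a stated capture rule. Up to T3, the named tool covers up to 7 occasions per youth in the TRT arm and 0 in the waitlist arm, and it omits activations at T1, T2 and T3 in both. The reported frequency is therefore incomplete and cannot support any statement about whether activations are more or less common with TRT than on waitlist. Pooling session and assessment triggers would leave unequal opportunity after randomisation, up to 9 against 2.

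This rests on the checklist being the only route the article names, on waitlist TRT starting after T3, and on full attendance for the upper limits. It does not show that the trial lacks harm-relevant data in both arms, or that a biased comparison is planned. The consequence is a safety figure that is open to misreading. The primary analysis is not affected.

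**What to change.** 1. Have the research team record each safety-protocol activation at T1, T2 and T3 in both arms, by participant ID, trigger (PHQ-9 item 9 or Cantril Ladder) and C-SSRS result.
2. Report by arm the number of youth with at least one activation at T2 or T3, using assessment-visit triggers only, with item 9 and Cantril Ladder triggers shown separately.
3. Report the checklist counts separately as a description of TRT sessions, and say that they are not a comparative safety result.

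The cost is one short log at assessments that already take place and a few lines of reporting text. The trigger scores are already held by participant, so only the activation and the C-SSRS result are new entries. Nothing in the care given changes. A standard adverse-event question at T2 and T3 in both arms would be a reasonable extra, but it is optional and the point does not depend on it.

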There is general agreement in the literature that trauma-focused cognitive behavioural therapy (TF-CBT) is the method of choice for treating PTSD and other internalising and externalising symptoms in trauma-exposed children and youth [15]. In Sweden, although it is the treatment of choice, TF-CBT is unfortunately not equally accessible or available in a timely manner for refugee children and youth due to resource constraints within specialised services. PTSD is associated with other mental health disorders such as anxiety, depression and substance use and, when untreated, it can lead to functional impairment in school and work, as well as increase the risk of suicide. For such a large group within society to experience mental health problems and associated poor health and integration outcomes without receiving the necessary support is unacceptable. There is a need to develop a stepped-care model with light-touch interventions tied into specialised services.

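### Adverse events are described as spontaneously reported, and a youth who does not trigger the C-SSRS is not directly asked about self-harm or a suicide attempt for most of the 20 weeks

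*Protocol article*

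**What the plan says.** Under Columbia-Suicide Severity Rating Scale (C-SSRS) Screen Version, the protocol article states: "Any spontaneously reported adverse events will be recorded and managed accordingly by a trained member of the trial team". It describes no scheduled adverse event question.

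The same section reserves the C-SSRS for participants who report "thoughts they would be better off dead (ninth item on PHQ-9) or ‘suffering’ on the Cantril Ladder (i.e. a score of 4 or below". The recall periods of the two triggers are given where the instruments are described. PHQ-9 items "are rated according to the frequency of their occurrence during the past 2 weeks". For the Cantril Ladder, "Respondents are asked to think about their life right now and place themselves on the ladder". C-SSRS items cover the past month, although item 6 as printed asks whether the youth has *ever* acted.

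Both triggers are given to both arms at T1, T2 and T3. The Design section places the later two at "post-intervention (T2; about 8 weeks after randomisation) and follow-up (T3; about 20 weeks after randomisation", and Participant timeline allows 1 week either side for T2 and 2 weeks for T3. There is one further check: "The Cantril Ladder will be administered at each TRT session to inform a safety protocol". Sessions run over 7 consecutive weeks in the TRT arm, and the waitlist arm starts TRT around week 20.

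The TiC-P is given to both arms at T1, T2 and T3. It asks about service contacts and school or work absence over a preceding period of unstated length. The Control arm section also relies on it to capture any services received.

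**The concern.** The Background section says that untreated PTSD can impair functioning "as well as increase the risk of suicide". The trial gives one arm a trauma-focused group programme that includes trauma narrative work, and the other arm waits about 20 weeks. Self-harm and suicide attempts are therefore events that a reader will want counted in both arms.

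The two triggers look back two weeks or not at all, while the assessments are 8 and 12 weeks apart. Take a youth who harms himself or herself in week 12 and has improved by T3. If item 9 is then 0 and the ladder is at 5 or more, the C-SSRS is not given, and the event reaches the data only if it is volunteered or happens to show as a service contact.

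Opportunity to volunteer also differs by arm. TRT youth meet group leaders weekly and complete the ladder at sessions, and waitlist youth have neither before T3. A low count of spontaneous reports could mean few events or few occasions to mention them, and a difference between arms could reflect contact rather than harm. No analysis plan can recover events that were not asked about.

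**Working it through.** **Inputs, all from the protocol article.** T2 = week 8 (7 to 9) and T3 = week 20 (18 to 22), from Participant timeline. PHQ-9 look-back = 2 weeks. Cantril look-back = 0. C-SSRS look-back = about 1 month, only after a trigger. TRT delivery = 7 weeks. Waitlist TRT starts around week 20, taken here as after T3.

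**The article's own interval.** T3 − T2 = 20 − 8 = 12 weeks, and 12 × 7 / 30.44 = 2.8 months. This agrees with the stated 3 months or so after delivery. The article gives no figure for how much of follow-up its enquiries cover.

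**A youth who does not trigger, nominal schedule.** Item 9 reaches back over weeks 6–8 and 18–20.

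- Waitlist arm, weeks 0–20: uncovered = T3 − (2 + 2) = 20 − 4 = 16 weeks.
- Both arms, T2 to T3: uncovered = (T3 − T2) − 2 = 12 − 2 = 10 weeks (weeks 8–18).

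**Across the visit windows.**

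| T2 | T3 | Weeks 0 to T3: T3 − 4 | T2 to T3: T3 − T2 − 2 |
|---|---|---|---|
| 7 | 18 | 14 | 9 |
| 9 | 18 | 14 | 7 |
| 7 | 22 | 18 | 13 |
| 9 | 22 | 18 | 11 |

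The ranges are 14 to 18 weeks and 7 to 13 weeks. Even this counts generously, because item 9 asks about thoughts, not about self-harm or an attempt.

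**A youth who triggers at both T2 and T3.** Taking the month as 4 weeks: 20 − (4 + 4) = 12 weeks over the whole period, and 12 − 4 = 8 weeks after T2. Item 6 as printed has no time limit, so an earlier act could be disclosed. An undated answer does not by itself place that act within the trial.

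**Extra checks in the TRT arm.** There are five core youth sessions, or seven with the introductory and follow-up sessions. The session ladder therefore adds 5 to 7 current-state checks, all within the 7 delivery weeks. None falls between T2 and T3, and none occurs in the waitlist arm before T3.

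**The case against.** The strongest case on the other side has five parts.

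*The TiC-P asks both arms about services.* This stands. A reader might infer that the TiC-P serves only the economic evaluation and that an admission would never be asked about. The Control arm section does not support that, since it uses the TiC-P to capture any services received. Whether an admission in week 12 is asked about at T3 depends on a recall length that the article does not state. The TiC-P is not described as harms capture, though, and it would miss self-harm without a service contact.

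*Youth who trigger are asked more.* This also stands. A reader might turn 16 of 20 weeks into a claim that about 8 in 10 waitlist events would be missed. The document does not support that. It gives no trigger rate for a population screened positive for PTSD symptoms, those who trigger get the past-month C-SSRS with its open-ended item 6, and a youth with a recent attempt may well be more likely to trigger.

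*The triggers are a safety screen, not a harms count, and no comparison of adverse events between arms is promised.* Correct. The point is not that a planned analysis is biased, but that the data collected could not carry a safety statement if one were made.

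*Symptom worsening is measured equally in both arms through the deteriorated class of the Reliable Change Index.* True, but that compares scores and does not record events. A youth who has recovered by T3 would not show.

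*The article condenses a fuller protocol.* The sentence does not say that spontaneous report is the sole route, and the safety protocol and SPIRIT checklist are not shown. This limits confidence. The article is not silent, however: it names spontaneous report, and no other route for adverse events.

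**Conclusion.** The point holds for youth who do not trigger the C-SSRS. As the article describes it, they are not directly asked about self-harm or a suicide attempt for about 16 of 20 weeks in the waitlist arm (14 to 18), or for about 10 of the 12 weeks between T2 and T3 in either arm (7 to 13). Youth who trigger are asked about the past month and, at item 6, without a time limit, but the answer is not dated to the trial. Spontaneous reports are not comparable between arms before T3, and a low count would not show safety.

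This rests on three assumptions: the stated visit windows are kept, waitlist TRT starts after T3, and the documents not shown contain no scheduled harms question. How many events would be lost cannot be estimated, because neither event rates nor trigger rates are given. The primary comparisons of symptom scores are unaffected. This is an inexpensive improvement to data collection and is worth making.

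**What to change.** Add one or two fixed items to the T2 and T3 online questionnaire for every youth in both arms, worded *since the last assessment*. They should cover self-harm or suicide attempt, and emergency or inpatient care for mental health. Set the TiC-P recall to the same interval and state it. Report these events by arm, list spontaneous reports separately, and state how many participants were assessed before the items were added. What follows a positive answer stays with the existing safety protocol.

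The cost is translation into the seven languages in which the outcome measures are initially available, an ethics notification, slightly longer forms in a group where poor literacy is anticipated, and some additional positive answers to handle. Randomisation began in April 2019, so participants already assessed would remain unasked. No extra visits are needed.
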